**Methods:**

This is a randomised cross-over trial in which a total of 30 participants will be randomly allocated to one of three different combinations of conditions: (i) Music only, (ii) tES only (control condition), (iii) Music + tES. The music intervention will consist of listening to an individually tailored playlist including familiar and self-relevant music together with fixed songs; concerning NIBS, tES will be applied for 20 minutes every day, 5 times a week, for two weeks. After these stimulations two weeks of placebo treatments will follow, with sham stimulation combined with noise for other two weeks. The primary outcomes will be clinical, i.e., based on the differences in the scores obtained on the neuropsychological tests, such as Coma Recovery Scale-Revised, and neurophysiological measures as EEG, collected pre-intervention, post-intervention and post-placebo.

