### Sample size determination

The effect size to be expected is uncertain as no study so far has implemented a combined intervention of music and electrical stimulation in DOC patients. We assume it to be in the medium-to large range (i.e., Cohen’s d between 0.5 and 0.8). We aim to achieve 80% power (*f* = 0.30) in a repeated-measures analysis of variance (*a* = 0.05, power (1-b) = 0.80) with condition as between-subject factor (tES combined with music stimulation vs. sham stimulation, and noise vs. music stimulation and sham stimulation), and time (pre-intervention, post-intervention and post-placebo), as within-subject factor. Power calculations (using G* Power 3) indicate that a valid sample size of *n* = 10 per group will result in 80% statistical power if the effect is *d* = 0.68, which is in the medium-to-large range. This results in a total sample size of *n* = 30.

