### Experimental design and procedures

The experimental paradigm is one of the main strengths of the study, as a randomized cross-over design will be used in this trial, including a treatment condition with electric brain stimulation combined with music listening and a placebo condition with sham brain stimulation combined with noise listening. The randomization of the participants to be included in each group will be done using the software “Research Randomizer” (www.randomizer.org). The randomization procedure will be performed by an independent researcher unrelated to the study. The randomization file will be saved in a password-protected online database. This independent researcher will enrol participants and will assign the patients to intervention groups. Both patients and examiner will be fully blinded.

Assessment times of outcome measures will be conducted at admission (T_0_), after the first weeks of post-intervention or post-placebo (T_1_), and after the second two weeks of post-intervention or post-placebo (T_2_) (Fig 1). Patients will be randomized into three groups depending on the order of the stimulation or placebo conditions:

Stimulation-Placebo: Patients receiving tES combined with music stimulation for 2 weeks, 1 week of wash out, then sham stimulation combined with noise (placebo) for other 2 weeks.Placebo-stimulation (combined tES and music): Patients receiving sham stimulation and noise (placebo) for the first 2 weeks, then 1 week wash out, and finally tES and music stimulation for other 2 weeks.Music-placebo: Patients receiving music stimulation and sham stimulation for 2 weeks, 1 week of wash out, then sham stimulation and noise (placebo) for another 2 weeks.

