### Data analysis

The SPSS 23.0 statistical software will be used for the data analysis. All the statistical hypotheses will be tested by two-side test, with statistically significant test level set at 0.05 and the confidence interval estimation to 95%.

The aim of our study is to evaluate the effects of the treatments in the various patient groups on the primary and secondary outcomes. Descriptive analysis of the data will allow us to identify the characteristics of the groups. Comparison of demographic and clinical characteristics of the groups will be performed using one-way ANOVA for continuous variables and the Chi-square test for categorical variables. Considering the crossover and longitudinal aspects, primary analyses will focus on behavioural changes at group level, comparing the treatments. Moreover, at the individual level, we will analyse the differences between pre-treatments and post treatments data.

As for the primary outcomes, we will measure the effects of the intervention on the following measures (two neurophysiological and two clinical and behavioral): (i) power spectra of frequency band extracted from the EEG recordings; (ii) auditory evoked responses, extracted from the EEG recordings; (iii) behavioural responses of DOC patients, measured through CRS-R.

Baseline characteristics and carryover effect will be analysed between the three sequences using ANOVA and chi-square test. By including the order of intervention as a covariate, we aim to determine whether the sequence in which participants receive the interventions impacts the observed outcomes. To assess the presence and magnitude of the washout effect, we plan to incorporate appropriate statistical methods into our analysis, such as comparing outcomes during the washout period to those observed during active treatment phases. To this end, we will use repeated measures ANOVA considering time (before, during, and after the washout) as the independent variable, with behavioral measurements as the dependent variables.

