To reach the goal of obtaining the above-described neurophysiological outcome measures, we will first pre-process the EEG data as follows. Data will be filtered to remove low frequencies not originating from the brain and to control for interference of the electric current, by means of a generic FIR filter, set up as a bandpass filter, with low cut-off at 0.5 Hz and high cut-off at 45 Hz (because of 50 Hz power line noise). Cerebral signals contaminated by artifacts will be identified and removed. Moreover, independent component analysis (ICA) will be performed. ICA algorithms will be used to detect and isolate artifacts, such as eye blinks, eye saccades, hearth, muscle, line noise, channel noise and others. In this way, the original signal will be decomposed into independent components: we will individuate and discard the components that picked up the artifacts activities and reconstruct a clear signal by using only the remaining components [70]. Further pre-processing steps will include epoch extraction, baseline removal, resampling, re-referencing to low temporal electrodes, and filtering.

To investigate whether slow neural oscillations are reduced and fast neural oscillations are increased post-treatment, the continuous EEG will first be divided into 2-seconds segments, transformed into the frequency domain with fast Fourier transform, inspected for myogenic artifact segments that will be rejected, and then averaged across the segments [71]. Any further exploratory analyses will be specified in the future publication of the findings of this study. Missing data will be treated according to Molenberghs et al. [72].

We will evaluate the music and electrical intervention effects on power spectra of frequency bands measuring EEG at rest and during music listening at T0 (pre-intervention), T1 (post-intervention) and T2 (post-placebo). To this end, we will compare the power spectra between rest and music conditions and across time. The ratio of fast (8–30 Hz, alpha and beta) to slow (2–8 Hz, delta and theta) oscillation amplitude at the midline electrodes (Fz, Cz, Pz, Oz) will be measured [70] and compared pre- and post- intervention using t-tests with cluster-based corrections of the multiple comparison problem. In the case of non-normal distributions, there will be applied mixed-effect ANOVAs or non-parametric equivalents to the parametric tests.

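### The EEG analysis calls T1 post-intervention and T2 post-placebo for every patient, although one sequence in three receives placebo first, and its pre-post tests state no contrast with placebo

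*Protocol article*

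**What the plan says.** The protocol article describes the visits in two incompatible ways.

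- **By sequence.** Under Experimental design and procedures, T1 and T2 may each follow active treatment or placebo; T2 is "after the second two weeks of post-intervention or post-placebo". The second of the three sequences is described as "Patients receiving sham stimulation and noise (placebo) for the first 2 weeks, then 1 week wash out, and finally tES and music stimulation". The other two sequences (combined then placebo, music then placebo) have placebo second.
- **Fixed for everyone.** Data analysis evaluates the EEG spectra at "T0 (pre-intervention), T1 (post-intervention) and T2 (post-placebo"). Sample size determination uses the same order in "time (pre-intervention, post-intervention and post-placebo), as within-subject factor". The abstract agrees: "After these stimulations two weeks of placebo treatments will follow".

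For the tests, the fast-to-slow EEG ratio is "compared pre- and post- intervention using t-tests with cluster-based corrections of the multiple comparison problem". Evoked-response amplitudes and latencies are likewise compared before and after intervention, with repeated-measures ANOVA and post-hoc paired t-tests over time. Both are listed as primary outcomes. For behaviour, Data analysis states an intention to compare treatments at group level. It then adds: "By including the order of intervention as a covariate", the plan aims to see whether sequence affects the outcomes. No period term is stated.

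**The concern.** If the fixed labels are followed, one third of patients enter the analysis with their active and placebo visits exchanged, and the effect is diluted. If a pre-post test is used, the comparison has no concurrent control. These patients are enrolled on admission to rehabilitation, receive daily physiotherapy and mostly take drugs meant to raise consciousness, so zero change over two weeks cannot be assumed. At stake is whether the EEG results estimate a treatment effect, a fraction of one, or the natural course.

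**Working it through.** **Inputs from the protocol article.** Three sequences of 10; two-sided alpha 0.05; detectable effect d = 0.68; stated f = 0.30; three visits.

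**Assumptions (the article gives no figures).** Visit SD 1 and correlation 0.5 between visits, so the SD of a change is √(2 × (1 − 0.5)) = 1; no carryover unless stated; drift s per block, common to all patients.

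**The plan's own figure.** With f = d/2 = 0.34, three groups, three visits, correlation 0 and the time main effect, λ = 30 × 3 × 0.34² = 10.4 on 2 and 54 df. Power is 0.809, so N = 30 is reproduced. This is not the only route: the group-by-time interaction with f = 0.34 and correlation 0.25 also gives N = 30. With the stated f = 0.30 and correlation 0, the time effect needs 39. The figure therefore does not show which test is intended.

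**1. Fixed labels, calendar visits, no drift.** Let dC be the effect of the combination and dM that of music.

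| Contrast | Combined first | Placebo first | Music first | Pooled |
|---|---|---|---|---|
| T1-T0 | dC | 0 | dM | (dC + dM)/3 |
| T1-T2 | dC | −dC | dM | dM/3 |

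With dC = dM = 0.68, T1-T0 = 2/3 × 0.68 = 0.45 and T1-T2 = 1/3 × 0.68 = 0.23. Simulated power is about 0.63 and 0.13. The sequence-by-period contrast on the two combined sequences alone (20 patients) has power 0.82. If only the combination works, pooled T1-T2 is 0.

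**2. Pre-post test, no treatment effect.** The noncentrality of the paired t-test is (drift/SD of change) × √n. Probability of a significant result:

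| Drift, SD of change | n = 10 | n = 30 |
|---|---|---|
| 0.2 | 8.8% | 18.5% |
| 0.3 | 13.6% | 35.5% |
| 0.5 | 29.3% | 75.4% |

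Aligning visits by condition but still testing post-active minus T0 makes this worse: 93% at a drift of 0.5 per block, because the placebo-first patients carry two blocks of drift.

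**3. Recoding by condition and contrasting with placebo.** Let π be the common T1-to-T2 change.

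- Combined minus placebo: (−10π + 10π)/20 = 0 bias. At π = 0.5 the simulated estimate is 0.68 for a true 0.68; with no effect, the pooled paired test rejects about 2.8% of the time.
- Music minus placebo, within patients: music is always first, so the bias is −π. At π = 0.5, 0.68 becomes 0.18.
- All active minus placebo: (−20π + 10π)/30 = −π/3. At π = 0.5, 0.68 becomes 0.51.

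**4. Contrasts that remove common drift.** With drift of 0.5 per block, the sequence-by-period contrast has type I error 0.050 and power 0.81. The three-group group-by-time interaction has type I error about 0.05 and power about 0.77.

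**The case against.** The strongest reply is that the ANOVA under Sample size determination also has condition as a between-subject factor. If the test is the group-by-time interaction, randomised sequences are compared with each other and common drift drops out, as step 4 shows. This stands as a possible reading. However, the article never names the interaction as the test, and it describes the factor by condition rather than by sequence.

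Next, combined versus placebo is free of period bias once visits are coded by condition received. Combined versus music can also be compared at T1 between two randomised groups that are both treated in the first block. Both points stand. They leave music versus placebo, any pooled active contrast and the pre-post tests unprotected.

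The order covariate is offered as protection. As a between-patient main effect it leaves a pooled within-patient time contrast unchanged. Whether it is also aliased depends on coding: it is if entered beside a three-sequence factor, but not beside a condition factor.

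An unseen analysis plan may well hold the period term, so its absence alone is no fault. The conflicting visit labels and the stated pre-post EEG tests are on the page and are not omissions. Finally, the error rates in step 2 rest on assumed drift and on a single t-test without the planned cluster correction.

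A reader might infer that every primary analysis loses the effect, or that the placebo comparison goes wholly unused. The article does not support that. It states a comparison of treatments for behaviour, and its EEG comparisons across time include the post-placebo recording.

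**Conclusion.** The point holds, most firmly for the EEG outcomes and for music versus placebo. The visit labels contradict the design for 10 of 30 patients. Taken literally, they reduce T1-T0 to two thirds and T1-T2 to one third of the effect, given equal effects, no drift and no carryover. Full cancellation is limited to pooling the two combined sequences, to the case where only the combination works, or to about 50% carryover with equal effects. The EEG pre-post tests credit any spontaneous change to treatment. Their error rate of about 18% to 75% at n = 30 depends on the assumed drift of 0.2 to 0.5 SD of the change and illustrates the scale; it is not a prediction. The CRS-R analysis is less affected, because a comparison of treatments is intended, but no drift-protected contrast is named for it either.

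**What to change.** Reconcile the visit descriptions in the abstract, Sample size determination, Experimental design and procedures, and Data analysis. Call T1 and T2 end of block 1 and end of block 2, and record the condition received in each block.

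For each primary EEG outcome and CRS-R, make the primary test a between-condition contrast with a period term. One form is a linear mixed model with condition received (combined, music, placebo), period (1, 2), the T0 value as covariate and a random patient effect, reporting combined-placebo, music-placebo and combined-music. It is identifiable because the two mirror-image combined sequences separate period from treatment. A named group-by-time or sequence-by-period contrast is an acceptable equivalent. Keep the pre-post t-tests as description only.

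The cost is revised analysis wording and one degree of freedom each for period and T0. SPSS fits the model, and neither new data nor a change to treatment is required.

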For the secondary outcome we will measure the effects of the treatments on caregivers’ depression, anxiety, psychophysiological symptoms, grief, strain and quality of life in order to evaluate the effectiveness in reducing the caregiver’s burden and psychological distress. Repeated-measures analysis of variance, as well as post-hoc paired *t*-tests will be conducted to assess the effects of the treatments over time on N1, P1, and P2 amplitudes and latencies, as well as level of consciousness. All these primary outcome variables will be analysed separately, using parametric or non-parametric tests for continuous and categorical variables respectively.

For the behavioural outcome, we expect an improvement of level of consciousness, as measured by CRS-R.

For the caregiver’s burden, we expect a positive effect of this new treatment protocol on caregiver’s wellbeing, with a decrease of psychological distress.

For neurophysiological outcome measures, we expect to obtain in DOC patients an increased EEG power spectrum in slow frequency bands, following a previous study [67] showing a generalized slowing in the theta or delta range associated with a significantly diminished α power. Power spectrum analysis is one of the standard methods used for quantification of the EEG. The power spectrum, namely the power spectral density, reflects the ‘frequency content’ of the signal or the distribution of signal power over frequency [68].

For the computation of the auditory evoked responses, the average EEG will be measured time-locked to the sound onset events in the music stimuli, after rejecting any residual noise exceeding 100 μV. P1 (fronto-central positive potential with ~50 ms latency), N1 (fronto-central negative potential with ~100 ms latency), and P2 (fronto-central positive potential with ~200 ms latency) amplitudes and latencies will be measured at the Fz and Cz electrodes [69], and compared pre- and post- intervention.

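### The only test named for the EEG fast/slow ratio, which summarises a primary outcome, is a pre/post t-test with no placebo, sequence or period term

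*Protocol article*

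**What the plan says.** All statements here are in the Data analysis section of the Protocol article unless another section is named.

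- **Outcome.** The first primary outcome listed is "i) power spectra of frequency band extracted from the EEG recordings". The ratio of fast (8–30 Hz) to slow (2–8 Hz) amplitude at four midline electrodes is the summary of those spectra that receives a named test.
- **Test of the ratio.** It will be "compared pre- and post- intervention using t-tests with cluster-based corrections of the multiple comparison problem". If distributions are not normal, mixed-effect ANOVAs or non-parametric equivalents replace the t-test. No placebo contrast is named for that case either.
- **Other comparisons of the spectra.** Intervention effects are to be evaluated by "measuring EEG at rest and during music listening at T0 (pre-intervention), T1 (post-intervention) and T2 (post-placebo"), and "we will compare the power spectra between rest and music conditions and across time". No test is given for this.
- **Comparison of treatments.** The text says "primary analyses will focus on behavioural changes at group level, comparing the treatments". The repeated-measures ANOVA is there "to assess the effects of the treatments over time on N1, P1, and P2 amplitudes and latencies, as well as level of consciousness"; spectral power is not in that list.
- **Evoked responses.** Besides that ANOVA, the text says that "amplitudes and latencies will be measured at the Fz and Cz electrodes [69], and compared pre- and post- intervention".
- **Design.** Under Experimental design and procedures, all three sequences contain two weeks of sham plus noise. Two sequences receive it last. In the third it comes first: "Patients receiving sham stimulation and noise (placebo) for the first 2 weeks". Assessments are at T0 (admission), T1 and T2, and none is listed after washout.
- **Sample size.** The Sample size determination section uses a repeated-measures ANOVA with condition between subjects and time within subjects, 10 per group and 30 in total.

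**The concern.** A pre/post test has no control. T0 is at admission, all patients receive daily physiotherapy, and most receive drugs meant to raise the level of consciousness (Music stimulation section). The Introduction says that slow frequencies dominate when consciousness is absent, that higher frequencies are preserved in the minimally conscious state, and that this state usually follows improvement from coma or the vegetative state. By the protocol's own account, then, the ratio should rise with recovery from any cause.

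If the plan is followed as written, a significant result on this primary measure could not be attributed to tES or music, although every patient also has a placebo period that would allow the controlled comparison. The named test also differs from the condition-by-time model used to justify the sample size.

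**Working it through.** **1. The plan's own figure.** The stated total of 30 can be reproduced, but only with a correlation that the text does not give. For a repeated-measures ANOVA with m measurements, noncentrality is λ = N f² m / (1 − ρ) for the within-subject and interaction terms.

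- f = 0.30, 3 groups, 2 measurements, interaction, ρ = 0.5 (assumed): λ = 30 × 0.09 × 2 / 0.5 = 10.8, df 2 and 27, power 0.800.
- f = 0.34 (d = 0.68, using d = 2f), 3 groups, 3 measurements, time effect, ρ = 0 (assumed): λ = 30 × 0.1156 × 3 = 10.4, df 2 and 54, power 0.809.

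The first is a condition-by-time model. Neither is the test named for the ratio. The point below does not depend on which was used.

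**2. Pre/post test with no treatment effect.** Inputs from the plan: two-sided α = 0.05 and 10 per group. Assumed: spontaneous gain g in between-patient SD units, and correlation ρ = 0.5 between visits. The SD of the change is √(2(1 − ρ)) = 1, so noncentrality = g√n / √(2(1 − ρ)) = g√n, with n − 1 df.

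| g | noncentrality, n = 10 | significant, n = 10 | significant, n = 30 (pooled) |
|---|---|---|---|
| 0.2 | 0.632 | 8.8% | 18.5% |
| 0.3 | 0.949 | 13.6% | 35.5% |
| 0.5 | 1.581 | 29.3% | 75.4% |

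A simulation of 20,000 runs (10 per sequence, equal drift per period) gave 8.9%, 13.6% and 30.1% for n = 10. The cluster-based correction is not modelled; it addresses multiplicity and does not remove drift.

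**3. Placebo-controlled contrasts in the same simulation.** Two were tried: the period-1 change in the stimulation-first versus the placebo-first sequence, and T1 minus T2 compared between those sequences. Both rejected in 4.9% to 5.1% of runs at every drift from 0 to 0.8 SD.

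**4. Can the comparison across time stand in as the control?** In a sequence where placebo comes last, T1 versus T2 is also earlier versus later. With no treatment effect and a drift of 0.5 SD per period, a paired test of T1 against T2 in 10 such patients rejected in 29% of runs. In the placebo-first sequence T1 follows placebo and T2 follows active treatment, the reverse of the labels in the Data analysis section. With no visit listed after washout, that sequence's pre-intervention value must be either T0, which spans the whole placebo period, or the end-of-placebo visit.

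**5. Power of the controlled contrasts at d = 0.68, ρ = 0.5.**

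- *Combination versus placebo* (two sequences, n = 20): half the between-sequence difference in mean T1 − T2. SE = ½√(1/10 + 1/10) = 0.224, noncentrality 0.68 / 0.224 = 3.04, df 18, power 82%, if there is no carryover.
- *Music plus sham versus placebo* (10 versus 10 at T1): SE = √(2/10) = 0.447, noncentrality 1.52, df 18, power 30%. Adjusting for T0 multiplies the variance by 1 − 0.5² = 0.75, giving noncentrality 1.76, df 17 and power about 38%.

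**The case against.** The case for the plan is that it does not ignore placebo EEG. The text just before the t-test lists T2 as post-placebo and compares spectra across time. The section opens by aiming to evaluate treatment effects on all primary and secondary outcomes, and it includes order of intervention as a covariate. An unseen full protocol or analysis plan could hold the exact contrast.

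Much of this limits the point without removing it. A reader might infer four stronger things that the text does not support:

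- *Placebo recordings are left out altogether.* They are not; they enter the comparison across time. That comparison has no test, no sequence or period term, and labels that misfit one sequence.
- *The evoked responses have the same gap.* The repeated-measures ANOVA named for N1, P1 and P2 refers to effects of the treatments over time, and the sample-size section gives that model a condition factor. Only the later pre/post phrase is loose.
- *The false-positive rate reaches 75%.* That needs all 30 patients pooled in one pre/post test. The text does not state this, and it would mix two interventions.
- *The ratio itself is listed as primary.* The power spectra are.

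The appeal to an unseen document does not settle the matter. The article does not leave the test open. It names one, and that one is uncontrolled. The order covariate addresses sequence effects and is not stated as an active-versus-placebo contrast for the ratio.

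**Conclusion.** The point holds for the spectral ratio. The one test named for it has no placebo, sequence or period term, and nothing else in the section supplies an interpretable control for it. With no treatment effect and an assumed gain of 0.2 to 0.5 SD, a group of 10 would show a significant change in about 9% to 29% of trials, against 5% for a placebo-controlled contrast.

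The size rests on assumed drift and correlation, since the documents give neither; with no drift the pre/post test keeps its 5%. The direction needs only some spontaneous or concurrent-treatment improvement, which the protocol's own description of these patients makes plausible. This should be corrected before analysis, because it decides whether a primary result can be attributed to the intervention.

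**What to change.** In the Data analysis section, replace the pre/post t-test of the ratio by the active-versus-placebo contrast with sequence and period terms, in line with the condition-by-time model under Sample size determination.

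- **Combination:** half the difference between the stimulation-first and placebo-first sequences in T1 minus T2, with the period-1 comparison of those sequences as a sensitivity analysis.
- **Music plus sham:** compare with the placebo-first sequence at T1, adjusted for T0, and state that power is low (about 30% unadjusted at d = 0.68).
- **Visits:** define them by the condition just received, not by fixed post-intervention and post-placebo labels.
- **Pre/post changes:** report as description, without a claim of treatment effect.
- **Evoked responses:** only align the pre/post phrase with the repeated-measures ANOVA of treatment effects already named.

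The cost is wording and code, with no new recordings. The pre/post p-values, which look more favourable, are given up as evidence. The crossover contrast relies on no carryover after a one-week washout, and the Introduction itself says that repeated stimulation makes the induced changes longer lasting. Persisting effects would pull that contrast towards zero. The period-1 comparison does not have this weakness, but its power is only about 30%.
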